### Main Intention and Objective

This study's main intention is to give awareness and authority to the community of health care professionals against cyberbullying by developing a Personalized Mobile Mental Health Intervention program (PMMH-I) in partnership with all health care providers. This partnership will seek to form alliances with public and private institutions to ensure the success and continuation of the program. The PMMH-I program will aim to reduce the psychometric properties of cyberbullying through awareness and adaptation of technology.

The main objective of this protocol is to develop and implement the PMMH-I program to decrease the psychometric properties of cyberbullying in the hospital-based setting in Malaysia. We hypothesize that the creation of PMMH-I programs will come about by executing a PMMH-I strategy that permits the fusion of global and local knowledge. PMMH-I promotes health care community development, thereby increasing social integration between different health care providers such as doctors, nurses, traditional and complementary medical practitioners, pharmacists, and other health care providers.

### Theoretical Approach

We will adopt the emotion reaction model (ERM) [15] as our theoretical framework, which allows researchers to explore the relationships among concepts of stressor, emotions, emotion regulators, and people who experience cyberbullying in the hospital setting in Malaysia. The ERM elucidates how emotions may produce an impact on people who experience cyberbullying in the current technological era. The adaptation of ERM depicted in Figure 1 posits the relationship between stressor, emotions, and people who experience cyberbullying, which is mediated by emotion reappraisal and emotion suppression.

**Figure 1 figure1:**
[figure not shown]
A proposed theoretical model of the emotion reaction model.

## Methods

### Ethics Approval

According to the local and national ethical instructions for research (the National Committee for Clinical Research) guidelines, this study did not require ethics approval.

### Data Sharing Statement

No data are available. All data relevant to the study are included in the manuscript.

### Study Plan

A hospital-based multimethod multi-analytic evidential approach is proposed, involving social and psychological health informatics. The project has been subdivided into 3 stages, starting with Phase 1, a prevalence study, followed by exploratory studies. Phase 2 consists of a quasi-experimental design, whereas the development of a prototype and their testing will be proposed in Phase 3. Flow diagrams for the research design are presented in Figures 2 and 3. A breakdown of our anticipated timeline for each phase of the study appears in Figure 4.

Each stage includes the use of quantitative and qualitative methods (mixed-method program), using SPSS (version 26.0; IBM Corp) and Stata (version 16.1; StataCorp) as tools for quantitative research, and NVivo (version 1.0; QSR International) and Atlas.ti (version 9.0.16; ATLAS.ti Scientific Software Development GmbH) for qualitative research.

**Figure 2 figure2:**
[figure not shown]
Research flow diagram.

**Figure 3 figure3:**
[figure not shown]
Flow diagram of the experimental design; PMMH-I: Personalized Mobile Mental Health Intervention.

**Figure 4 figure4:**
[figure not shown]
Gantt chart of study-related activities.

### Phase 1: Multimethod Multi-Analytic Evidential Approach

#### Objectives

Phase 1 will consist of the identification and analysis of the problem. The duration of this phase will be 6 months and will include knowledge development about workplace cyberbullying among TCM practitioners.

#### Prevalence Study

The specific objectives of this study include (1) evaluating the overall prevalence rate of workplace cyberbullying and its related psychological impacts (depression, anxiety, and stress) on TCM practitioner; (2) understanding the measures associated with various forms of workplace cyberbullying on age, gender, and frequency; and (3) understanding the measure associated with workplace cyberbullying on perpetrators responsible for workplace cyberbullying. The current research will be a survey-based online cross-sectional prevalence study. TCM practitioners are considered a hard-to-reach population; thus, we will conduct a nonprobability snowball sample of 1023 adults (3% precision, 95% confidence level) according to the number of TCM practitioners, which was approximately 15,000 in 2011 [16]. The Hamilton Depression Scale (HAM-D) [17], the Hamilton Anxiety Scale (HAM-A) [18], and the clinical anger scale [19] will be used to assess the psychological impact on TCM practitioners. The Cyberbullying Questionnaire (CBQ) and a short version of a cyberbullying behavior questionnaire (CBQ-S), adapted from Jönsson et al [20], will be used to identify the prevalence among TCM practitioners; these selected questionnaires were already validated in Sweden and the US adult population [20]. The prevalence will also investigate the association with moderating variables (age and gender). Perpetrators of cyberbullying will also be assessed in the specific identification of the prevalence of workplace cyberbullying using the CBQ and CBQ-S questionnaires. The sampling method to understand perpetrator effects in the prevalence will similarly be addressed. The survey will also include a socioeconomic assessment, including education, income, home characteristics, and commodities. The survey will be conducted online due to the current pandemic situation caused by COVID-19, following the CHERRIES guidelines given by Gunther Eysenbach [21].

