## Introduction

### Background

Suicidal behavior, depression, loneliness, anxiety, and somatic symptoms are among the most common effects of cyberbullying experienced by students [1] and adolescents [2]. There is a huge psychological impact (ie, depression) on people who experience workplace bullying from coworkers, such as nurses [3-6], health care providers, and employers [7], especially among women. The prevalence of cyberbullying among first-year trainee doctors who reported experiencing it at least 1 time was 46.2% [8]. Another study found a high prevalence rate (28%) of cyberbullying among a diverse workforce sample in the United States [9].

Malaysia has a high mobile penetration rate due to thriving e-commerce [10]. The problematic use of smartphones can lead to addiction; increased use of mobile phones in India has led to an increase in technology addiction [11,12]. This addiction leads to depression, anxiety, stress, and self-esteem issues [13]. A school-based study identified a strong correlation between pathological internet use and cyberbullying in Greece [14]. However, there is a lack of evidence that pathological mobile use could lead to an increase in cyberbullying in the workplace. Most published studies, systematic reviews, and interventions are limited to cyberbullying at school, colleges, universities, or the young population.

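### The 3% precision stated for the prevalence survey is a simple-random-sampling margin that a nonprobability snowball sample of 1023 does not have

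*Protocol article*

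**What the plan says.** The Prevalence Study section (Methods, Phase 1) gives its first objective as "evaluating the overall prevalence rate of workplace cyberbullying" and related psychological impacts. The sample is described in one sentence: "we will conduct a nonprobability snowball sample of 1023 adults (3% precision, 95% confidence level". The number is tied to a population count: "according to the number of TCM practitioners, which was approximately 15,000 in 2011". The reason for the sampling method is that "TCM practitioners are considered a hard-to-reach population".

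The section gives no expected prevalence, formula or design-effect allowance, and it does not say that the margin is conditional on random sampling.

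The Exploratory Study section does the same for its survey. It sets a sample of 384, recruited by convenience and snowball methods, and gives it 5% precision at 95% confidence.

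**The concern.** A margin of error at a stated confidence level is a claim about repeated sampling: 95% of samples drawn by the design would give an estimate within that distance of the population value. This requires known inclusion probabilities. A snowball sample has none, because entry depends on who the first contacts are, how many colleagues each knows and whom they choose to invite. Respondents may also resemble the people who referred them. Referrals among practitioners could plausibly run through shared workplaces, so a workplace outcome could cluster along referral chains. That last step is an inference; the article does not describe the referral paths.

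The quantity affected is the survey's main result. The first item under Research Questions asks about the current status of workplace cyberbullying among TCM practitioners in Malaysia, which is a population-level question. Someone who takes the ±3 points at face value would think the answer better determined than the design allows.

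**Working it through.** **Inputs from the article**
- Sample size n = 1023, margin e = 0.03 and 95% confidence, so z = 1.96 (Prevalence Study).
- Population N ≈ 15,000 in 2011 (Prevalence Study).
- For sensitivity, prevalences of 46.2% in trainee doctors and 28% in a US workforce sample (Background).

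**Assumptions, not in the article**
- Prevalence p = 0.5, the conventional worst case.
- Design effects (deff) of 1.5 to 4, for illustration.

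**1. The plan's own number**
- Without finite-population correction: n0 = z²p(1−p)/e² = 1.96² × 0.25 / 0.03² = 1067.1.
- With correction: n = n0 / (1 + (n0 − 1)/N) = 1067.1 / (1 + 1066.1/15,000) = 996.3, rounded up to 997.
- The stated 1023 is 26 larger, or 26/1023 = 2.5% of the stated figure.
- Solving the same formula for n = 1023 gives N of about 24,750; N = 25,000 gives 1023.4.
- With p = 0.462 the requirement is 991, and with p = 0.28 it is 814. Neither explains 1023.

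**2. What 1023 delivers under simple random sampling**
- Without correction: 1.96 × √(0.25/1023) = 3.06 points.
- With N = 15,000: 3.06 × √((15,000 − 1023)/(15,000 − 1)) = 3.06 × 0.965 = 2.96 points.

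So "3% precision, 95% confidence level" is met on paper, for a simple random sample.

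**3. How much departure the margin tolerates**

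The half-width grows with √deff, so ±3 points is exceeded once deff is above (3.00/2.96)² ≈ 1.03. The tolerance depends on p. At p = 0.28 the corrected half-width is 1.96 × √(0.28 × 0.72/1023) × 0.965 = 2.66 points, and the limit is (3.00/2.66)² ≈ 1.28.

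**4. Illustration (p = 0.5, N = 15,000, with finite correction)**

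| Assumed deff | Half-width at n = 1023 | n needed for ±3 points |
|---|---|---|
| 1 | ±2.96 | 997 |
| 1.5 | ±3.6 | 1,447 |
| 2 | ±4.2 | 1,869 |
| 3 | ±5.1 | 2,639 |
| 4 | ±5.9 | 3,323 |

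Half-widths are 2.96 × √deff. The last column puts deff × 1067.1 in place of n0 in the corrected formula. No row includes selection bias, which a larger n does not reduce.

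**5. The Exploratory Study**

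1.96² × 0.25 / 0.05² = 384.2, the uncorrected figure. With N = 15,000 it would be 375. This margin is also a simple-random-sampling one attached to a convenience and snowball sample, and the two Phase 1 surveys do not use the same population basis.

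**The case against.** The strongest reply is that the article is open about its method: it calls the sample nonprobability and gives a reason for it. The margin may be no more than shorthand for how the number was chosen. The survey is descriptive and has no part in the comparison of intervention and control hospitals. Most of this stands, and it limits the weight of the point. It does not rescue the claim, because the article attaches the margin to the snowball sample itself and never calls it nominal.

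A reader might infer four stronger things that the article does not support.

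- **That 1023 is a material arithmetic error.** It is not. It is slightly larger than 15,000 requires and meets the nominal target. The count is also approximate and dated 2011, while the Results section says the survey began in July 2020, so exact reproduction is too strict a test.
- **That the protocol should state ±4 to ±6 points instead.** No design effect is given in the article, so that would replace one unsupported figure with another.
- **That Phase 2 rests on this prevalence.** The Phase 2 section says only that it follows Phase 1. It measures its own baseline in the hospitals, and the intervention is designed from a review of reviews, focus groups and a workshop. No Phase 1 prevalence is shown to feed a Phase 2 calculation.
- **That the result will be published as nationally representative with a ±3-point interval.** The article does not say so.

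**Conclusion.** The point holds as a misstatement of precision. The article gives its prevalence survey a margin that belongs to a design it does not use. Under simple random sampling with p = 0.5 and N = 15,000 the margin would be ±2.96 points, which leaves almost no room: a design effect of about 1.03 uses it up, or about 1.28 if the prevalence were 28%. How far the real uncertainty exceeds ±3 points cannot be fixed from the article. The ±4.2 to ±5.9 points for design effects of 2 to 4 only illustrate sensitivity, and selection bias comes on top.

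The choice of 1023 as a recruitment target is not faulted, nor is snowball sampling for this population. That 1023 matches a population of about 25,000 better than the cited 15,000 is a minor question of traceability.

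**What to change.** 1. In the Prevalence Study section, keep 1023 as the target. Either delete the 3% precision claim or say that it is nominal and would hold only under simple random sampling.
2. State that the prevalence will be reported as a non-probability estimate, and that any nominal interval shown with it does not account for clustering along referral chains or for selection bias.
3. Make the same change to the 5% precision stated for the 384 in the Exploratory Study section.
4. State the expected prevalence and population size behind each number. For the first survey, say whether 1023 came from about 25,000 or was a rounding-up from 997.

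The cost is a few sentences and a less favourable statement of precision, with no extra participants. Recording who referred whom and each respondent's network size, with respondent-driven-sampling weights, would be an optional strengthening. It rests on recruitment assumptions that the article does not claim to meet, and because the survey began in July 2020 it may be possible only for later respondents. The wording and reporting changes do not depend on it.

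### The online prevalence survey assigns the interviewer-rated HAM-D and HAM-A with no rater or self-report version described, and names no stress scale although stress is in its first objective

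*Protocol article*

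**What the plan says.** All of the instrument choices at issue stand in the Prevalence Study section of Phase 1.

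- **Objective 1:** "evaluating the overall prevalence rate of workplace cyberbullying and its related psychological impacts (depression, anxiety, and stress) on TCM practitioner".
- **Instruments for psychological impact:** "The Hamilton Depression Scale (HAM-D) [17], the Hamilton Anxiety Scale (HAM-A) [18], and the clinical anger scale [19] will be used".
- **Mode:** "The current research will be a survey-based online cross-sectional prevalence study", and later in the same section "The survey will be conducted online due to the current pandemic situation caused by COVID-19, following the CHERRIES guidelines".
- **Sample:** "nonprobability snowball sample of 1023 adults (3% precision, 95% confidence level"), set with reference to "the number of TCM practitioners, which was approximately 15,000 in 2011".
- **Validation:** one sentence, placed after the two cyberbullying questionnaires (CBQ and CBQ-S) and referring to them: "these selected questionnaires were already validated in Sweden and the US adult population". Nothing comparable is said of the HAM-D or HAM-A.

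Research question 2 makes depression, anxiety and stress the factors on which the intervention is judged before and after. The Phase 2 section on the quasi-experiment names only the CBQ and CBQ-S for its baseline. The Results section says that the prevalence survey began in July 2020.

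**The concern.** The HAM-D and HAM-A, in their standard form, are filled in by a trained rater who interviews the person and judges each item. An online questionnaire passed along by referral normally has no such rater, so respondents would apply observer items to themselves. The resulting number has the name of a Hamilton score but an error structure that nobody has stated. Severity bands that belong to the rated form would not carry over.

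Two conclusions are at stake. One is any statement about how common or severe depression and anxiety are among these practitioners. The other is the association of those states with cyberbullying, which error in the outcome can weaken or distort. Separately, stress is part of objective 1 but has no scale in the set, while an anger scale is included although the objective does not mention anger.

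**Working it through.** **Step 1. The plan's own figure.** The inputs are the stated 3% precision, 95% confidence and a population of about 15,000. A proportion of 0.5 is assumed, as none is given.

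- n0 = z² p(1−p)/d² = 1.96² × 0.25 / 0.03² = 1067.1
- With finite population correction: n = 1067.1 / (1 + 1066.1/15000) = 996.3, so 997

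The stated 1023 is 26 higher (26/1023 = 2.5%), which is close enough. At n = 1023 the 95% half-width at p = 0.5 is 1.96 × √(0.25/1023) = 3.06 points, or 2.96 with the correction. The stated precision is about right as sampling error under simple random sampling. The present point does not depend on this figure.

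**Step 2. Instrument against mode.**

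| Item | What the article gives |
|---|---|
| Depression measure | HAM-D, version not stated |
| Anxiety measure | HAM-A, version not stated |
| Stress measure | none named |
| Mode | online survey, following an e-survey guideline |
| Interviewer, rater training, telephone or video rating | none described |
| Validation for this mode | none stated for the HAM-D or HAM-A |
| Case cut-off or severity band | none stated |

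That the standard Hamilton scales are interviewer-rated is a basic property of the named tools; the article does not say it. The absence of a rater is inferred from the online format. Rating about 1,000 people one by one would be a major part of the work, and one would expect it to be mentioned.

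**Step 3. What self-completion could do to a rate.** The document gives no accuracy figures, so this is illustration only. With true rate p, sensitivity Se and specificity Sp against a rated score:

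- observed rate = p·Se + (1−p)(1−Sp)
- bias = (1−p)(1−Sp) − p(1−Se)

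| Assumed p | Se | Sp | Observed | Bias (points) |
|---|---|---|---|---|
| 0.20 | 0.90 | 0.90 | 0.18 + 0.08 = 0.26 | +6 |
| 0.20 | 0.80 | 0.80 | 0.16 + 0.16 = 0.32 | +12 |
| 0.20 | 0.60 | 0.95 | 0.12 + 0.04 = 0.16 | −4 |
| 0.50 | 0.90 | 0.90 | 0.45 + 0.05 = 0.50 | 0 |

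The sign changes with the inputs, so no single range describes this study. What does hold in general is that n does not appear in the bias formula. Quadrupling the sample would halve the half-width from 3.06 to 1.53 points and leave the bias as it was.

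**Step 4. Associations.** If the error is the same in bullied and non-bullied respondents, a true difference in rates is multiplied by Se + Sp − 1. That is 0.8 for 0.90/0.90, 0.6 for 0.80/0.80 and 0.55 for 0.60/0.95. A true 10-point difference would read as 8, 6 or 5.5 points. If the error differs between the groups, the direction is open.

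**Step 5. Where else the scales appear.** Nowhere. The Exploratory Study lists emotions, stressors, perpetration, victimization and appraisal constructs. The Phase 2 baseline and the Phase 3 post-test name the CBQ and CBQ-S. Research question 2 therefore has no named depression, anxiety or stress measure in the phase that tests the intervention.

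**The case against.** The strongest reply is that the article is silent on version and administration, and silence is not proof. A condensed article may leave both to a fuller document, and the sources cited for the two scales cannot be seen here. This stands to the extent that self-completion of the standard form must be labelled an assumption. It does not remove the point, because the article does state instruments, mode and validation, and as stated they do not fit together.

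A second reply is that the Hamilton scales are there to assess impact, while the CBQ and CBQ-S supply the prevalence, and that no cut-off is given anywhere. This also stands in part. Objective 1 can be read as the prevalence of the impacts, or as the prevalence of cyberbullying plus an assessment of its impacts. Harm to case rates is therefore conditional on such rates being reported.

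A reader might infer more than the document supports:

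- **That depression will be overstated by some 6 to 12 points.** Those figures follow from chosen inputs, and other plausible inputs give −4 or 0.
- **That the Hamilton scales must be replaced in the exploratory survey and Phase 2.** Neither section plans to use them, so there is nothing to replace.

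Finally, the missing stress scale has nothing to do with who does the rating. It is a separate gap in the same list of instruments, visible without any knowledge of the Hamilton scales, and adds no weight to the question of mode.

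**Conclusion.** The concern holds in a limited form. The Prevalence Study section pairs two scales that are interviewer-rated in their standard form with an online survey for which no rater or self-report version is described, and it leaves stress, a listed impact, without a scale. Assuming that the standard versions are self-completed, the scores have unknown error against rated scores and do not support Hamilton severity categories or case rates. The direction and size of any bias in rates cannot be derived from the document, and the planned 3% precision does not cover it because it reflects sampling error alone.

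The conclusion rests on two things that the article does not state in words: that the standard versions are meant, and that nobody rates the respondents. If either is wrong, a sentence saying so settles the Hamilton part. The missing stress measure, and the lack of any named measure of the three factors in Phase 2, would remain.

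**What to change.** **Prevalence survey (running since July 2020).** Report the HAM-D and HAM-A items as self-completed symptom scores only, with no Hamilton severity categories and no case rates. If trained remote raters or a validated self-report version were in fact used, state that in the Prevalence Study section instead. Say plainly that stress was not measured, or name the scale that measured it.

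**Phase 2.** Add one scale validated for self-completion that yields depression, anxiety and stress scores, so that research question 2 has an outcome. Use it unchanged at baseline and at both follow-ups, in intervention and control hospitals alike.

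**Cost.** A few sentences for the running survey and a slightly longer questionnaire in Phase 2. The prevalence-survey scores will not be directly comparable with the Phase 2 scores, and the report should say so.

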#### Exploratory Study

The purpose of the exploratory study is to understand the moderating and mediating factors of workplace cyberbullying by using the ERM on TCM practitioners [15]. The specific questions of this study include the following: (1) What are the relationships between emotions, workplace stressors, cyberbullying perpetration, cyberbullying victimization, and control appraisal, reappraisal, and suppression? (2) What effects do demographic factors have on emotions, workplace stressors, cyberbullying perpetration, cyberbullying victimization, and control appraisal, reappraisal, and suppression? The survey will be conducted using a convenience method, with a sample size of 384 (5% precision, 95% confidence level). A structural equation model will be developed, and each construct will be discussed. A snowball sampling method will be used to approach the target population. There will be a lucky draw at the end of the exploratory study on the participants; the 10 winners of the draw will receive an electronic power bank.

This procedure was selected due to a hard-to-reach study population and a study undertaken during the COVID-19 pandemic.

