### Research Questions

We aim to explore the following 4 research questions in this study: (1) What is the current workplace cyberbullying status among Traditional Chinese Medicine practitioners (TCM) in Malaysia? (2) What is the pre- and postefficacy of the Personalized Mobile Mental Health Intervention (PMMH-I) on the prevalence of measurable factors (ie, depression, anxiety, and stress) in workforce cyberbullying on TCM practitioners? (3) What are the moderating and mediating factors of workplace cyberbullying on TCM practitioners? (4) What is the technological feasibility of implementing the integrated PMMH-I as a component of routine hospital-based systems?

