#### Quasi-experiment with Nonequivalent Pretest–Post-test Control Group Design

The study design for this stage is quasi-experimental, in which the groups are nonrandomized into intervention and control groups and selected purposively. This study will be conducted in public hospitals and private hospitals located in Malaysia. All hospitals are eligible to participate. The selection of hospitals will be randomized for the implementation of the interventions. The randomization of hospitals will be performed by online statistical computing web programming to generate the randomization schedule [22]. The current methodology will help reduce selection bias in the study.

This intervention study will be conducted on TCM practitioners specifically. A baseline assessment will be done, in the intervention and control hospital, to measure the burden of bullying and its correlates using the CBQ and CBQ-S. This stage will begin after the investigation of prevalence and exploratory research. First, baseline information will be collected within 3 months, and then the intervention will be monitored twice after a regular period of 6 months in order to monitor the consistency of the intervention program.

The intervention program will be designed and finalized after (1) a systematic review of systematic reviews of previously published literature on bullying and the effectiveness of antibullying intervention programs; (2) the conducting of focus group discussions with TCM practitioners, patients, and other health care providers (to explore the perceptions, beliefs, and suggestions regarding bullying prevention programs); and (3) the conducting of a consultation workshop with all the stakeholders. The bullying intervention program (BIP) will pretest among 50 participants, which will include health care providers, TCM practitioners, and patients. The multicomponent hospital-based intervention strategy will be administered at 3 levels: (1) patients, (2) TCM practitioners, and (3) other health care providers. All the data of participants in this study will be password-protected and safe using Microsoft OneDrive. The recruitment of participants will follow the same procedure described for the exploratory study and prevalence study.

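### The single-occasion exploratory survey can report associations consistent with the emotion reaction model, but cannot establish mediating factors as research question 3 and the study's purpose imply

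*Protocol article*

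**What the plan says.** All references are to the protocol article.

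- **Research Questions**, question 3 of four: "What are the moderating and mediating factors of workplace cyberbullying on TCM practitioners".
- **Theoretical Approach**: the link between stressor, emotions and people who experience cyberbullying is posited as one "which is mediated by emotion reappraisal and emotion suppression".
- **Exploratory Study**, purpose: "The purpose of the exploratory study is to understand the moderating and mediating factors of workplace cyberbullying by using the ERM on TCM practitioners".
- **Exploratory Study**, data: "The survey will be conducted using a convenience method, with a sample size of 384 (5% precision, 95% confidence level"). Snowball sampling is also named.
- **Exploratory Study**, analysis: "A structural equation model will be developed, and each construct will be discussed".

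No repeat measurement is described for this survey. The design label appears only for its sister study (Prevalence Study): "The current research will be a survey-based online cross-sectional prevalence study". That the exploratory survey is also single-occasion is an inference, but it is the only reading its section supports.

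Repeated measurement appears in Phase 2: "baseline information will be collected within 3 months, and then the intervention will be monitored twice after a regular period of 6 months". The instruments named for the Phase 2 baseline are the CBQ and CBQ-S. No measure of stressors, emotions, reappraisal or suppression is named there, and no mediation analysis is planned there.

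**The concern.** Mediation is a claim about order and cause: the stressor changes emotion regulation, which then changes cyberbullying. If all three are reported on one occasion, the order is supplied by the analyst's diagram and not by the data. A structural equation model drawn in the opposite direction can fit equally well. A shared influence, such as low mood or a habit of answering all items alike, can produce an indirect path when no mediation exists.

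The reverse order is not far-fetched here, because the article's own text supports it. The Theoretical Approach runs from stressors and emotions towards cyberbullying. The Background lists depression, loneliness and anxiety among the effects of cyberbullying, and the Prevalence Study treats depression, anxiety and stress as its psychological impact.

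What is at stake is the answer to one of four research questions. If the plan is followed as written, reappraisal and suppression could be reported as mediators on evidence that does not distinguish this from the alternatives.

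**Working it through.** **1. The plan's sample size.** With n = z²p(1−p)/d², z = 1.96, d = 0.05 and p = 0.5 (assumed; not stated): n = 3.8416 × 0.25 / 0.0025 = 384.2. The stated 384 is reproduced. It is a precision size for one proportion and has no bearing on mediation.

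**2. Forward and reversed order.** Let X be the stressor, M emotion regulation and Y cyberbullying, all standardised, with each path equal to r.

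- Forward (X to M to Y): corr(X,M) = r, corr(M,Y) = r, corr(X,Y) = r².
- Reversed (Y to M to X): corr(Y,M) = r, corr(M,X) = r, corr(X,Y) = r².

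The correlations are identical, so no analysis of them can choose between the two. Simulation at n = 384, fitting the forward model, agrees. At r = 0.2 the indirect path was significant in 95% of samples under either truth, with a mean indirect effect of 0.04 under both. At r = 0.3 to 0.5 the rate was 100% under both.

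**3. Common cause, no mediation.** One unmeasured cause gives X, M and Y the same pairwise correlation r. The indirect path is called significant when both its parts are, each at 5% two-sided (joint-significance test; the article names no test). Approximately:

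- X to M: z₁ = r√(n−2)/√(1−r²)
- M to Y given X: partial correlation p = r/(1+r), z₂ = p√(n−3)/√(1−p²)
- P(significant indirect path) ≈ P(|Z+z₁| > 1.96) × P(|Z+z₂| > 1.96), with Z standard normal

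| r | z₁ | first part | p | z₂ | second part | product | simulated |
|---|---|---|---|---|---|---|---|
| 0.05 | 0.98 | 0.165 | 0.048 | 0.93 | 0.154 | 0.025 | 2.5% |
| 0.10 | 1.96 | 0.502 | 0.091 | 1.78 | 0.429 | 0.215 | 22% |
| 0.15 | 2.97 | 0.843 | 0.130 | 2.57 | 0.728 | 0.614 | 60–61% |
| 0.20 | 3.99 | 0.979 | 0.167 | 3.30 | 0.910 | 0.891 | 88–89% |
| 0.30 | 6.15 | 1.000 | 0.231 | 4.63 | 0.996 | 0.996 | 99% or more |

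**4. Would the Phase 2 occasions resolve it?** A lagged model was simulated on three waves at n = 384 (assumed; the article gives no Phase 2 size), with all constructs assumed measured at each wave: X at wave 1, M at wave 2 adjusted for M at wave 1, and Y at wave 3 adjusted for Y at wave 2.

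- True order reversed (lagged paths 0.3 and 0.5): false mediation in 0.2% and 0.4% of samples.
- No causal path but a stable unmeasured common cause: false mediation in 71%, 96%, 99% and over 99% of samples at r = 0.2, 0.3, 0.4 and 0.5.

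Three waves therefore deal with reversed order, but do not by themselves remove a stable common cause.

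**The case against.** The strongest reply is that the article claims little. The study is labelled exploratory, its aim is to understand, its first specific question concerns relationships, and the theory section only posits mediation. Nowhere is a significant indirect effect said to prove anything, and model details may sit in a fuller document. This is fair as to tone. But mediating factors are the object of both a main research question and the study's stated purpose. The number of measurement occasions is a design property, and no later analysis choice can put time order into one-occasion data. The label does not change that.

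Three stronger readings are tempting, and none is supported:

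- **That the three Phase 2 occasions could settle mediation.** The Phase 2 section names only the CBQ and CBQ-S at baseline. Its groups are nonequivalent and are treated between assessments, and the intervention may act on the proposed mediators. The simulation above shows that a common cause would survive an ordinary lagged model.
- **That the survey would nearly always find mediators.** This depends on correlations the article does not give. At r = 0.10 the rate is 22%, and at 0.05 it is 2.5%.
- **That the intervention will be built on the fitted Phase 1 model.** The article lists a review of systematic reviews, focus groups and a stakeholder workshop as the steps before the program is finalised. That Phase 2 follows the exploratory study is sequencing. The intervention is described as an adaptation of the published emotion reaction model, not of the survey's fitted paths.

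**Conclusion.** The concern holds in limited form. The protocol article sets out to understand mediating factors from a structural equation model on what can only be read as a single-occasion survey of 384 people. That design cannot tell mediation from reversed order at any correlation. With no mediation and a common cause, it gives a significant indirect path in about 2.5% of samples at r = 0.05, rising through 22%, 60% and 88% to 99% at r = 0.10, 0.15, 0.20 and 0.30.

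These rates assume equal pairwise correlations, normal variables, one mediator and a joint-significance test at 5%. The conclusion about order needs none of these assumptions beyond the single occasion. The defect lies in what Phase 1 is said to deliver; fitting the model is reasonable as description.

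**What to change.** **Needed.** In Research Questions (question 3) and in the purpose of the Exploratory Study, state that the Phase 1 structural equation model reports associations consistent with the emotion reaction model and does not establish mediators or their order. Cost: a few words.

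**Optional.** Measure stressors, emotions, reappraisal and suppression at the Phase 2 baseline and both later assessments. Analyse them with a lagged model that includes:

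- terms for study arm and hospital;
- person-level (random-intercept) terms or measured confounders;
- a sensitivity analysis for unmeasured confounding.

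This would address time order but would not fully rule out a common cause, and the report should say so. Cost: a longer questionnaire at three assessments. Whether the Phase 2 sample would suffice cannot be judged, because its size is not stated.

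Before relying on those assessments, reconcile their timing. The Phase 2 design section has two monitoring points at 6-month intervals after a baseline collected within 3 months. The Results section has a 4-month baseline and two 4-month intervention periods.
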